### 6.2.3 SECONDARY OUTCOME MEASURES

- **Disease-specific-survival** – (RADICALS-RT only)
- **Freedom from treatment failure:** PSA progression when on androgen deprivation
- **Clinical progression-free survival:** Clinical progression of prostate cancer or initiation of non-protocol hormone therapy or death from prostate cancer.
- **Overall survival:** Death from any cause
- **Non-protocol hormone therapy:** Initiation of hormone therapy other than that randomised
- **Treatment toxicity:** Incidence of severe toxicity or serious adverse events. Radiotherapy treatment planning data is required to understand the cause of treatment toxicity.
- **Patient reported outcomes:** See [Section 13.1](#) for details
- **Freedom from biochemical progression:** Where a biochemical progression event is defined as a PSA level of  $\geq 0.4$  ng/ml following radiotherapy or a PSA level of  $> 2.0$  ng/ml regardless of prior radiotherapy.

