| Study Design             | 
RADICALS is an international, multi-centre, open-labelled, randomised controlled trial in prostate cancer. It is a trial with two separate randomisations for overlapping patient groups.
 
One randomisation was performed within 22 weeks after radical prostatectomy (RADICALS-RT or the Radiotherapy Timing Randomisation; see section 4 for eligibility criteria). In this, patients were randomised between early post-operative radiotherapy and deferred post-operative radiotherapy (for PSA failure).
 
The other randomisation was performed shortly before the administration of post-operative radiotherapy and concerns the addition of hormone therapy (RADICALS-HD or the Hormone Duration Randomisation). In this, patients were randomised between radiotherapy with no hormone therapy, radiotherapy with short-term hormone therapy or radiotherapy with long-term hormone therapy. Randomisation between all three arms was encouraged but patients could be randomised just between short-term and long-term hormone therapy or just between short-term hormone therapy and no hormone therapy.
 
Patients joining the RADICALS-RT were encouraged to join RADICALS-HD (if and when they had RT) but were not required to do so. Patients were required to consent separately to each randomisation. Patients who had not taken part in RADICALS-RT could still enter RADICALS-HD alone if post-operative radiotherapy was clinically indicated, either early post-surgery or in the deferred setting for PSA failure.
 |

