## TRIAL DURATION

The trial was originally planned to address these questions over 12-13 years with 5½ to 6½ years of accrual and around 7 years of further Follow-up. The IDMC has advised that overall event rates have been much lower than anticipated. This prompted a change of primary outcome in the RADICALS-RT comparison (changed in protocol V4.0 from disease-specific survival to freedom from distant metastasis). The IDMC subsequently advised that event rates are lower still (without reference to comparative data by arm).

Following updated projections in 2019, the IDMC and TSC also supported the proposal for the change in primary outcome for RADICALS-HD from disease-specific survival to metastasis free survival, based on the findings from the IcECaP study. This proposal was also approved by the trial funder.

The patient group is men with non-metastatic adenocarcinoma of the prostate who have had a radical prostatectomy. Treatment duration within the trial will range from zero months (i.e. a proportion of patients, maybe 60%, allocated to deferred radiotherapy will never need it) to 24 months (for patients allocated long-term hormone therapy). Follow-up is required every 4 months for 2 years, every 6 months from 2 to 5 years and then annually. This broad patient group has a good long-term prognosis and full, long-term Follow-up data are essential to understand the impact of these treatments. For more details refer to [Section 7.1](#).

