The Early Prostate Cancer (EPC) Program accrued 4400 men who had radical prostatectomy and were randomised between observation versus 2 years adjuvant bicalutamide 150 mg. At a median follow-up of 7.4 years, there was no evidence of a difference in overall survival, but the data remain immature in this predominantly low-risk population. This very large trial serves to underline that at present there is no proven role for adjuvant hormone therapy alone after radical prostatectomy (23-24). It is important to note that this trial will not answer the questions RADICALS is posing, since the indications for post-operative radiotherapy were not specified, and because salvage treatment was delayed until clinical (rather than biochemical) progression was observed.

A small trial of adjuvant hormone therapy in men with pathologically involved pelvic lymph nodes, EST-3886, was stopped after 98 patients had been accrued because an overall survival advantage for adjuvant treatment was observed (25-26).

One question that has received little or no attention to date is that of the optimum duration of hormone therapy in patients receiving post-operative radiotherapy to the prostate bed. The surveys of UK urological and oncological opinion (12-13), mentioned above, found that the use of hormone therapy was variable, with most urologists recommending radiotherapy alone. Only 35% of urologists and 34% of oncologists were using hormone therapy in combination with radiotherapy. Among those oncologists who used hormone therapy in combination with post-operative RT, short-term hormone therapy (defined as 3 to 12 months) was recommended by 31% of respondents, long-term hormone therapy (defined as >12 months) by 25%, while the remaining 44% used both short-term and long-term hormone therapy depending on the characteristics of the patient. Similarly, in the survey conducted in planning the RADICALS trial, respondents were using none, short-term and long-term hormone therapy for a median (quartiles) of 50% (0%, 90%), 0% (0%, 50%) and 10% (0%, 33%) of their patients receiving adjuvant post-operative radiotherapy and 50% (0%, 90%), 13% (0%, 50%) and 5% (0%, 30%) of their patients receiving salvage post-operative radiotherapy i.e. there is significant variation in clinical practice.

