#### 4.1.1 EARLY POST-OP RADIOTHERAPY

Patients allocated to early radiotherapy to the prostate bed will start treatment within approximately 2 months of entering into RADICALS-RT and ideally within 26 weeks after surgery. Radiotherapy will be according to guidelines given in [Section 6.1.3](#). Patients allocated early post-operative radiotherapy can also enter RADICALS-HD if they wish: this is encouraged. Alternatively, the use of hormones can be decided by the responsible investigator. Radiotherapy will be delayed by 2 months, up to 8 months after surgery, if the patient is due to receive hormone therapy.

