### 6.2 OUTCOME MEASURES

RADICALS considers a number of primary and secondary outcome measures; all outcome measures are relevant to both trial randomisations unless otherwise stated. All outcome measures will be timed from the relevant randomisation.

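### Read literally, clinical PFS in RADICALS-RT counts permitted hormone therapy given with radiotherapy as progression, which counts against early RT unless such use is much lower with early than with deferred RT

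*Combined protocol and SAP*

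**What the plan says.** Section 6.2.3 (repeated in the Trial Summary) defines non-protocol hormone therapy as "Initiation of hormone therapy other than that randomised". Clinical PFS is defined as "Clinical progression of prostate cancer or initiation of non-protocol hormone therapy or death from prostate cancer", so every non-protocol HT event is also a clinical PFS event.

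The Outcome Measures list in the Trial Schema names both as secondary outcomes of RADICALS-RT. Section 6.2 adds that "all outcome measures are relevant to both trial randomisations unless otherwise stated", and that "All outcome measures will be timed from the relevant randomisation".

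RADICALS-RT allocates early or deferred RT only (Trial Summary; section 3.1.1). Joining RADICALS-HD is optional. For early-arm men who do not join, section 4.1.1 says: "Alternatively, the use of hormones can be decided by the responsible investigator". Section 4.1.2 also allows for HT with deferred RT, by delaying RT when HT is due.

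Section 4.1.1 has early-arm RT starting about 2 months after randomisation, with a further 2-month delay if HT is due. For the other arm, the Trial Duration section expects that a proportion, "maybe 60%, allocated to deferred radiotherapy will never need it".

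Section 6.5 leaves analysis detail to a separate SAP, which was not among the documents available for this review.

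**The concern.** The definition works in RADICALS-HD, where HT is what is randomised. In RADICALS-RT no HT is randomised, so the test of whether HT differs from the allocated HT has nothing to refer to for a man who never joins RADICALS-HD. Taken at its word, HT that section 4.1.1 allows with his RT is a non-protocol HT event, and so a clinical PFS event, on the day it starts. Nothing in the available text exempts it.

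The effect is unequal by design. Concurrent HT can only be given to men who have RT. Almost all the early arm is due RT soon after randomisation, while a minority of the deferred arm has it, and later. Clinical PFS would then partly measure how often and how soon RT was given. The standalone HT outcome would mix HT planned with RT and HT started later for relapse, which mean different things to a reader weighing early RT.

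**Working it through.** The plan gives no event rate, power or target effect for clinical PFS or non-protocol HT, so there is no stated figure to reproduce. The check is of direction and plausible size.

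**Inputs**
- *r*, share of the deferred arm ever given RT: 1 − 0.60 = 0.40 (Trial Duration), varied from 0.2 to 0.6.
- *x*E and *x*D, share of irradiated men in the early and deferred arms who have investigator-chosen HT outside RADICALS-HD: not in the documents; assumed.
- *b*, true clinical PFS event risk by a fixed follow-up time, equal in both arms: 15%, assumed.
- All early-arm men receive RT. HT choice is independent of true progression.

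**Formulas**
- Early-arm events: 1 − (1 − *b*)(1 − *x*E)
- Deferred-arm events: 1 − (1 − *b*)(1 − *r*·*x*D)
- Apparent HR (early v deferred): ratio of the logs of the two event-free proportions. With no true effect it should be 1.

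**Worked case, 10% in both arms.** Early: 1 − 0.85 × 0.90 = 23.5%. Deferred: 1 − 0.85 × (1 − 0.4 × 0.10) = 1 − 0.85 × 0.96 = 18.4%. HR = ln(0.765)/ln(0.816) = 1.32. With 1396 men randomised 1:1 (698 per arm), the HT starts counted are about 70 early and 28 deferred.

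| *x*E | *x*D | *r* | Early events | Deferred events | Apparent HR |
|---|---|---|---|---|---|
| 5% | 5% | 0.4 | 19.3% | 16.7% | 1.17 |
| 10% | 10% | 0.4 | 23.5% | 18.4% | 1.32 |
| 20% | 20% | 0.4 | 32.0% | 21.8% | 1.57 |
| 10% | 10% | 0.2 | 23.5% | 16.7% | 1.47 |
| 10% | 10% | 0.6 | 23.5% | 20.1% | 1.19 |
| 10% | 18% | 0.4 | 23.5% | 21.1% | 1.13 |

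**The last row** uses the planning survey in section 1.4. Median shares of patients were 0% short-term plus 10% long-term HT with adjuvant RT, and 13% plus 5% with salvage RT. Adding medians is crude, and these are shares of respondents' patients, not of trial men outside RADICALS-HD. HR = ln(0.85 × 0.90)/ln(0.85 × 0.928) = ln(0.765)/ln(0.7888) = 1.13.

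**Direction.** The early arm has more such events whenever *x*E > *r*·*x*D, that is, when *x*E/*x*D exceeds about 0.4. The survey ratio is 10/18 = 0.56. If RADICALS-HD uptake were similar in both arms, both shares would shrink together and the ratio would stand.

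**Timing.** These formulas ignore when events occur. A simulated Cox model with 20% true events by 10 years, early RT at about 4 months and deferred RT spread to reach 40% by 10 years gave HRs of 1.17 (5% in both arms), 1.31 (10% in both) and 1.15 (10% v 18%). For 10% in both arms and 20% true events, the formula gives ln(0.80 × 0.90)/ln(0.80 × 0.96) = 1.24, so earlier event times in the early arm add to the distortion.

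**The case against.** The strongest reply is that the outcome is called non-protocol HT, and section 4.1.1 allows investigator-chosen HT inside the protocol's own treatment guidance. Permitted HT could naturally be read as protocol HT. Strictly, even HT allocated in RADICALS-HD is not randomised by RADICALS-RT, so no one can apply the phrase word for word here. The meta-analysis outcome list also has a separate item for time to salvage HT, so the trialists know the distinction. This stands as evidence of likely intent. It does not remove the problem: the written test is what was randomised, not what was permitted, and two careful analysts of an open-label trial could code the same man differently.

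Other points also stand:
- The separate SAP may already contain the exemption.
- For the standalone outcome, more and earlier HT under an early-RT policy is partly a real treatment burden, so the bias argument is strong only for the clinical PFS composite.
- If HT is chosen for men who would progress anyway, counted events replace true ones. With full overlap, both arms stay at 15% and only the timing shifts.
- Only secondary outcomes are touched. Neither freedom from distant metastasis nor freedom from biochemical progression contains HT.

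A reader might take section 1.4, "Only 35% of urologists and 34% of oncologists were using hormone therapy in combination with radiotherapy", as showing that about a third of irradiated men would be affected. That is a share of clinicians, not of patients, and cannot be used as *x*.

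**Conclusion.** The concern holds for the clinical PFS composite in RADICALS-RT. Applied as written, the definition counts permitted concurrent HT as progression, more often and earlier in the early arm. The direction is against early RT unless HT use with early RT is below about 0.4 times that with deferred RT, which the planning survey does not suggest.

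The size is not known. With 15% true events per arm, *r* = 0.4, no true effect and HT choice independent of risk, the apparent HR is about 1.3 at 10% use in both arms and about 1.13 at 10% v 18%. It is smaller if HT goes to men who would progress anyway. The documents give neither the share of RADICALS-RT men irradiated outside RADICALS-HD nor their HT use.

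A reader might infer that the sponsor plans to count such HT as progression, or that both outcomes will show spurious harm of a known size. The documents support neither: the intent is unclear, the SAP is unseen, and part of any difference in the standalone outcome would be real. This is a definition worth correcting, not a threat to the primary result.

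**What to change.** - **Definition.** For RADICALS-RT, define non-protocol HT as HT started other than (a) by RADICALS-HD allocation or (b) as a planned course with the man's first post-operative RT. Use this inside clinical PFS. State in advance how an HT start date is matched to an RT course, and settle it without reference to comparative data. If the separate SAP already says this, align the protocol wording.
- **Sensitivity analysis.** Report clinical PFS without the HT component.
- **Description.** Report concurrent HT with RT separately by arm as treatment received, so that the burden is visible.

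The cost is one definition and one extra analysis; clinical management does not change. There are two caveats. HT begun with deferred RT follows PSA failure, whereas HT begun with early RT does not, so exempting both is a judgement; the sensitivity analysis covers it. And section 4.5 records dates for study treatment without saying that investigator-chosen HT is included, so the sponsor should confirm that the CRFs capture its start date and allow it to be matched to RT dates.

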### 6.2.4 EARLY REPORTING OF BIOCHEMICAL OUTCOMES

In early 2018, based on the number of primary outcome events in the control arm of the RADICALS-RT comparison, the target number of events was not forecast to occur until 2025. This is several years later than originally expected due to the low event rate. Two other randomised controlled trials (RCTs), RAVES and GETUG 17, also address the question of deferred RT and are planning to report in 2018/2019. The ARTISTIC project is a pre-planned individual patient data meta-analysis, combining RAVES, GETUG-17 and RADICALS-RT. The RADICALS TMG therefore agreed, in February 2018, to publish the Freedom from biochemical progression results of RADICAL-RT to coincide with the other two trials, and enable a timely meta-analysis.

## 6.3 SAMPLE SIZE

### 6.3.1 BASIC ASSUMPTIONS

The original sample size calculations were performed using the `-art-` package in Stata 9(31). The sample size re-calculation was performed in Stata 11.1. using version 1.0.8 (date 24mar2010) of `-art-`, including `-artsurv-` for the main calculation and `-artpep-` for variations. In terms of accrual and follow-up, we assume 5½ to 6½ years of recruitment, attaining a constant rate of accrual by 3 years after initiation of the trial in RADICALS-RT; a steady rate of accrual may be reached slightly later in time in RADICALS-HD as the rate may not peak until patients allocated deferred radiotherapy in RADICALS-RT start to experience biochemical failure. After recruitment, we assume a further 7 years of Follow-up. Clinically, we assume that, in RADICALS-RT, we should only be interested in treatment options with an absolute increase in 10-year freedom-from-distant-metastasis of 5%. In RADICALS-HD, we should only be interested in treatment options with an absolute increase in 10-year metastase-free survival of 6%, at least.

The sample sizes have been calculated separately for the two randomisations because of potential variation in the underlying assumptions, an uncertain proportion of patients joining RADICALS-RT

and RADICALS-HD and some uncertainty about accrual rates. A number of scenarios relating to trial recruitment and assumptions have been calculated and are reported elsewhere but are available upon request. Selected scenarios are reported here.

### 6.3.2 RADICALS-RT SAMPLE SIZE

In the patients suitable for this randomisation, the control arm is assumed to be deferred radiotherapy i.e. radiotherapy at PSA relapse.

When the trial was originally designed, there was uncertainty about the likely event rate but it was anticipated that a modest absolute effect in the order of 5% would be required to convince clinicians to adopt adjuvant radiotherapy for all patients. The original sample size calculations anticipated that around 2,600 patients would need to be recruited over 5½ years and followed-up for a further 7 years in order to obtain 80% power to detect an improvement from 70% to 75% or 90% power to detect an improvement from 80% to 85%.

From SWOG 8794 and EORTC 22911, the proportion of patients free of distant metastases at 10 years is estimated to be 90%. We would look to test whether adjuvant RT can improve this to 95% (hazard ratio 0.487), which is seen as the minimum clinically significant improvement required to routinely introduce adjuvant RT to this patient population; this mirrors the size effect observed in SWOG 8794. This is tested using the superiority design. With 80% power, a two-sided 5% significance level, accrual lasting 5½ years (reaching peak accrual rates after 3 years) and a further 7 years of follow-up, we would need to recruit 1,063 patients in order to observe 66 distant metastases events. This sample size assumes that 30% of patients are lost to follow-up and around 30 patients per month randomised from 30 months onward. Therefore, the target sample size will be reduced from 2,600 to around 1,063 patients. This assumes that 30% of patients are lost to follow-up between 5 and 10 years.

If the peak accrual is lower, at around 25 patients per month, accrual would be extended by 1 year, to around 6½ years and around 1,160 patients would be randomised; this should address the question with the same power and in the same overall timescale.

### 6.3.3 RADICALS-HD SAMPLE SIZE

Patients would be suitable for this randomisation if they are planned for post-operative radiotherapy regardless of whether this is the early or deferred setting.

There is some uncertainty in the baseline disease-specific survival (DSS) rate for patients receiving early RT and for patients receiving deferred RT. It is assumed that patients receiving early radiotherapy do at least as well as patients receiving deferred radiotherapy, timed from randomisation to RADICALS-HD. There is also uncertainty over the proportion of early and deferred patients that would join the trial; it is assumed that at least as many patients in the deferred setting will be randomised, if not two to three times more.

Since the trial was designed in 2006, further information on the baseline estimates of disease specific survival have become available from similar patient cohorts, including data from the RTOG 9601, SWOG 8794 and EORTC 22911 trials. These provide useful estimates as they are clinical trials and recruited partly during the PSA era; such information was not previously available when RADICALS-HD was designed.

Sites and patients are encouraged to join the three-way randomisation of no-HT vs STHT vs LTHT in RADICALS-HD as this is the most efficient for the trial. However, it has become apparent that the three-way randomisation is less well supported than either of the two separate potential two-way randomisations: no-HT vs STHT and STHT vs LTHT. These are each clinically important questions and

the trial will address both. It will not be possible to address one of the originally envisaged comparisons: no-HT vs LTHT with any reasonable degree of power, although the comparison will be performed. Therefore, there are two main comparisons in RADICALS-HD:

1. RT-only (no-HT) vs RT + short-term hormone therapy (STHT)
2. RT+ short-term HT (STHT) vs RT + long-term HT (LTHT)

It is assumed that patients who enter RT+STHT vs RT+LTHT comparison have a slightly higher risk of a disease event than patients who enter RT-only vs RT+STHT comparison because the clinician assumes that some HT is required; therefore, their 10 year DSS rate is estimated as being lower.

#### **6.3.3.A COMPARISON: NO-HT vs RT+STHT**

##### **Original power calculations:**

It was estimated that DSS would be 85% at 10 years in patients on the no-HT arm. This superiority trial is testing whether addition of STHT to RT can improve this to 91% (hazard ratio HR=0.58). A total of 1263 patients (128 events) in a comparison of no-HT vs STHT would allow for 80% power to detect an increase of 6% in 10-year DSS with a 3% significance level (accounting for the multiple use patients who join the three-way randomisation). This assumes that 30% of patients are lost to follow-up. Peak accrual would be around 31 patients per month in the comparison of no-HT vs RT+STHT.

If peak accrual is lower, at around 25 patients per month, accrual would be extended by 1 year to around 6.5 years and around 1368 patients would be randomised; this should address the question in the same timescale with the same power.

##### **Updated power calculations:**

The primary outcome measure of RADICALS-HD was amended from DSS to MFS after peer review in 2019 and without any reference to accumulating, comparative data. At this point, recruitment was already completed with 1480 patients in the 0 vs 6 months comparison. It is estimated that MFS will be approximately 80% at 10 years in patients allocated to the no-HT group. The 0 vs 6 months comparison would have over 80% power, with a two-sided 5% alpha, to detect an absolute increase in MFS of 6%, from 80% in the no-HT group to 86% (HR=0.67) in the short-HT group. Approximately 200 MFS events are anticipated for this analysis.

